### Ethical aspects

All clients who are considered for the study will receive a clear explanation that they have the right to refuse participation in the study and that their participation is entirely voluntary. Service users who decline to participate will be eligible for treatment if applicable and will not be disadvantaged in any manner. The participants will be given a clear explanation that their participation is entirely voluntary and is not part of their routine care at the hospital. All participants have the right to withdraw from the study at any time, and this will be clearly conveyed to them verbally and in writing.

Patients who agree to participate will be given a clear explanation that they may or may not receive the intervention drug, topiramate. Apart from adding topiramate, other management aspects will be similar in both the intervention and control groups. None of the study participants will be provided with any financial reimbursement for participating. The study has ethical clearance from the ethical review committee of the Faculty of Medicine, University of Kelaniya, Ragama, Sri Lanka. The trial is registered in the Sri Lanka Clinical Trials Registry [31].

Apart from topiramate therapy, all other treatment decisions for both groups will be independent of the study. The patients will be assessed by doctors who are not part of the research group for independent opinion and management. However, any addition or omission of any psychotropic or other medication is to be reported to the researchers because this could have a significant impact on the weight of the patient. In addition, the collected information is to be recorded under specific codes and is to be kept confidentially on password-protected institutional computers. Only the principal investigator will have direct access to data, and other researchers will have access to it as necessary for a limited period.

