Sri Lanka is a developing nation in South Asia with a population of 21 million people. The Colombo North Teaching Hospital in Ragama is the only tertiary care hospital in Gampaha District, which, with a population of more than 2 million people, is the second most populous district in the country [19]. The 1387-bed hospital has a specialized psychiatric service with inpatient and outpatient facilities. The mental health services in Sri Lanka lack physical as well as human resources, and the psychiatrist-to-population ratio is low [20].

The country-wide prevalence of schizophrenia in Sri Lanka is not known. However, the duration of untreated psychosis in patients with schizophrenia in Sri Lanka has been found to be almost 3 years, which is extremely long compared with more affluent countries of the world [21]. In a previous study conducted in Colombo North Teaching Hospital, a higher prevalence of substance use was found among patients with schizophrenia. In this study conducted in 2013, tobacco, cannabis, alcohol, and betel use were seen among 24%, 20%, 11%, and 9%, respectively, of patients with schizophrenia presenting to the hospital outpatient psychiatry clinic [22]. In a later study conducted in 2014 with a larger sample of patients with schizophrenia at the same hospital, researchers found that 43% of the 400 study participants were cigarette smokers, and 88% of them were dependent on nicotine [23]. Betel chewing has been seen at a higher rate among patients with schizophrenia in this setting, which could predispose them to health risks such as oropharyngeal carcinoma [24]. In addition, drivers with schizophrenia and other psychotic disorders treated with psychotropic medications at the Colombo North Teaching Hospital were detected to have more collisions and less earnings per day than a control group [25]. Because community outreach services are at a minimally developed level, many patients with schizophrenia presenting to this hospital are prescribed intramuscular depot antipsychotics. In a study conducted among 481 outpatients with schizophrenia in 2007, 23% had satisfactory compliance, and the compliant patients had low relapse rates at 15%, compared with 65% of the poorly compliant group, during a period of 1 year [26].

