### Data collection

Subsequently, using an interviewer-administered questionnaire, a senior registrar in psychiatry will gather preliminary information from the participant and direct the participant to a research assistant. The research assistant is a medical doctor specifically trained in obtaining anthropometric measurements from an adult patient. The research assistant will obtain the measurements mentioned in the data record form and will record the initial assessment details. The anthropometric measurements will include height, waist circumference, body weight, and skinfold thickness. In addition, a detailed assessment of eating patterns, daily energy intake, and physical exercise will be conducted. Afterward, the participant will be assessed by a consultant psychiatrist of the research team using the Brief Psychiatric Rating Scale (BPRS), and the symptom score will be recorded [30]. The anthropometric and clinical assessments are to be carried out in the same manner in every monthly visit during the 3-month study period. Details on the age of onset of the disorder, number of relapses, past and current treatments, and the presence of medical disorders will be gathered from the patients and, if necessary, from their relatives for clarification, as well as from the clinic records and past diagnosis cards.

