### Study outcomes

The primary outcome of the study is changes from baseline values in body weight, waist circumference, and/or skinfold thickness (or BMI) at three follow-up time points. The points of measurement are after the first, second, and third months of the trial period. The secondary outcome is the change in the symptom score according to the BPRS assessed at three follow-up time points. The symptom scores are assessed only to determine a possible exacerbation of symptoms, even though worsening with topiramate has not been reported in the past.

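### The only exacerbation measure is mean BPRS at monthly visits, and the medication-reporting rule omits dose changes, so some treated exacerbations can be missed or excluded

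*Protocol article*

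**What the plan says.** The Study outcomes section defines the measure: "The secondary outcome is the change in the symptom score according to the BPRS assessed at three follow-up time points". It also gives the purpose: "The symptom scores are assessed only to determine a possible exacerbation of symptoms". The Sample size estimation section repeats that purpose. Data management compares means between arms at each assessment by independent t tests. Data collection fixes the timing: "The anthropometric and clinical assessments are to be carried out in the same manner in every monthly visit during the 3-month study period".

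On concomitant treatment, Ethical aspects says that, topiramate apart, "all other treatment decisions for both groups will be independent of the study". It then sets the reporting duty: "any addition or omission of any psychotropic or other medication is to be reported to the researchers". The reason given is "because this could have a significant impact on the weight of the patient"; symptom worsening is not mentioned. The Eligibility criteria section adds that a participant who is given a new psychotropic during the study is taken out of the final analysis.

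Two other channels exist, both under Adverse effects. Serious adverse effects that need admission are referred for expert opinion, and the treatment code can be broken. Participants can also tell the research team about any troublesome symptom, at the clinic or by telephone.

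**The concern.** The question the secondary outcome is meant to answer is about individuals: did anyone get worse because topiramate was added? The planned answer is a difference in group means on three dates. A worsening that is treated and has settled before the next visit does not raise the score on any of those dates. One that is still visible at a visit is averaged with everyone else.

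The treatment given for a worsening would be the natural second source of information, but the stated rules weaken it in two ways. A dose increase of an existing antipsychotic falls outside the reporting duty. A new psychotropic falls inside it, but leads to the participant being excluded from the analysis. Both can happen with the protocol followed exactly. What is at stake is whether an excess of exacerbations on topiramate would show in the reported results.

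**Working it through.** **Where each kind of exacerbation goes under the stated rules**

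| How it is handled | Must it be reported? | Does it enter the symptom comparison? |
|---|---|---|
| Dose increase only, settled by the next visit | No | As an ordinary score |
| Dose increase only, still present at the visit | No | Diluted in the group mean |
| New psychotropic | Yes (Ethical aspects) | No: data removed (Eligibility criteria) |
| Admission | Referral route if judged a serious adverse effect | No defined exacerbation outcome |
| Participant reports the symptom | Voluntary | No defined exacerbation outcome |

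**How many relapses to expect.** The protocol gives no 3-month figure. The Background section describes 481 outpatients with schizophrenia in 2007, of whom 23% had satisfactory compliance; "the compliant patients had low relapse rates at 15%, compared with 65% of the poorly compliant group, during a period of 1 year".

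- Pooled yearly risk: 0.23 × 0.15 + 0.77 × 0.65 = 0.535.
- Three months at constant hazard: 1 − (1 − 0.535)^0.25 = 0.174.
- All participants like the compliant group: 1 − 0.85^0.25 = 0.040.
- All participants like the poorly compliant group: 1 − 0.35^0.25 = 0.231.
- Weighting the two quarterly risks instead: 0.23 × 0.040 + 0.77 × 0.231 = 0.187.

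With 90 randomised this is 0.174 × 90 = 15.7 relapses (range 3.6 to 20.8). The plan's own sizing is 72 / (1 − 0.20) = 90, which reproduces and leaves 36 analysed per arm. That gives 0.174 × 36 = 6.3 relapses per arm (range 1.4 to 8.3). These are all relapses, however treated.

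**How far the mean moves.** If topiramate adds a proportion *e* of participants with relapse, each raises the BPRS by *r* points, and a fraction *v* is still visible at the visit, the mean shifts by *e* × *r* × *v*. The protocol gives none of these values, nor a BPRS SD. Assumed here: *e* = 0.10 or 0.20, *r* = 10 or 20, *v* = 1 or 0.5, SD 8 or 12, with 36 per arm and two-sided 5% tests. Power counts rejections in the harmful direction only, so it can fall below 5%.

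| Excess relapse | Mean shift, all visible | Power | Mean shift, half visible | Power | Power if every relapse is counted as an event |
|---|---|---|---|---|---|
| 10 points | 1 to 2 | 5.4% to 18.4% | 0.5 to 1 | 3.7% to 7.6% | 17.1% (17% vs 27%) |
| 20 points | 2 to 4 | 10.5% to 56.4% | 1 to 2 | 5.4% to 18.4% | 47.6% (17% vs 37%) |

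If all 45 per arm are counted, the event powers become 20.4% and 56.8%.

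**Precision of a count.** With a true risk of 0.174 in both arms and 45 per arm, the half-width of the 95% interval for the difference is about 1.96 × √(2 × 0.174 × 0.826 / 45) = 0.157, or roughly ±16 percentage points.

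**The case against.** The strongest reply is that this leans on the silence of a condensed article. Data collection mentions a record form that is not shown and lists current treatments and number of relapses among the details gathered. Doses may therefore be captured, and a responder-type analysis could sit in an analysis plan. Change on a rating scale at monthly visits is also a conventional symptom outcome, and the protocol says this outcome is not essential to its main goal.

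Part of this stands: a form might record doses. But the protocol does not say those details are collected again at follow-up, and the reporting duty is written out and drawn too narrowly, not merely left undetailed. An analysis plan cannot recover events that nobody was required to report.

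A reader might infer several stronger things that the documents do not support:

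- **That treated relapses leave no trace.** Added drugs are reported, and admissions and troublesome symptoms have routes. The gap is limited to worsening handled by dose increase alone, without admission or participant report.
- **That about 16 of 90 relapses would be hidden.** That figure is all expected relapses. Trial participants, who must have capacity to consent and who keep daily intake records, may also differ from the 2007 cohort.
- **That worsening would be cancelled by average improvement.** It can be: 10% worsening by 18 points and 90% improving by 2 gives 0.1 × 18 − 0.9 × 2 = 0. Those numbers are chosen to sum to zero and say nothing about likelihood.
- **That the weight comparison is distorted by unreported dose differences.** The protocol links weight to drugs added or omitted and does not discuss dose. No direction or size can be given.

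**Conclusion.** The point holds in a limited form. The measure does not fit its sole stated purpose well. Exacerbations managed only by a dose increase between visits can be missed or diluted, and those managed with a new psychotropic are excluded by rule. About 17% of participants might relapse in 3 months (range 4% to 23%), assuming constant hazard and a population like the 2007 outpatients. The share treated by dose change alone is not given anywhere, so the size of the hidden part cannot be stated.

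It would go too far to say that the trial cannot answer its safety question as planned but could with an event count. Under the assumptions above the count has power of only 17% to 48% at 36 per arm, and when every relapse is still visible at the visit the mean comparison can do as well (up to 56%). The advantage of the count is that it shows events the mean can hide and keeps participants whom the exclusion rule would remove. No judgement is made here on which dose changes clinicians should make.

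**What to change.** 1. **Ethical aspects:** extend the reporting rule to *addition, omission or change of dose*. This concerns recording only and places no restriction on treatment.
2. **Study outcomes:** beside the BPRS means, report the number of participants per arm with an exacerbation, with a confidence interval for the difference. Count a participant with any of: existing antipsychotic dose increased for symptoms, antipsychotic added for symptoms, psychiatric admission, or a BPRS rise from baseline above a threshold fixed before unblinding.
3. **Eligibility criteria:** state that this count covers all randomised participants, including those whose data would otherwise be removed after a new medication. Without this, the added-antipsychotic component would be deleted by the protocol's own rule.

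The cost is protocol wording and one line on the monthly record form; usual medication is already written on the clinic prescription card. The downside is a small count with a wide interval (about ±16 percentage points above), so it should be presented as descriptive safety information, not as a powered test.

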### Data management

The data collected will be entered using Excel software (Microsoft, Redmond, WA, USA) and will be analyzed using OpenEpi software. At the end of the study period, calculations of mean weight differences (primary outcome) and BPRS symptom scores (secondary outcome) will be done at each assessment time point. The means will be compared for differences using independent *t* tests, and other relevant statistical analyses will be carried out.

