## Background

Schizophrenia is a psychiatric disorder with positive, negative, affective, and cognitive symptoms. It is associated with a shorter lifespan and higher mortality than that of the general population [1]. Many of the premature deaths among patients with schizophrenia are due to cardiovascular disease [2].

Second-generation antipsychotics are increasingly used for the treatment of schizophrenia [3], probably due to less extra pyramidal side effects being seen when using atypical antipsychotics [4]. However, atypical antipsychotics are associated with more metabolic adverse effects, such as weight gain, than the older typical antipsychotics [5].

The metabolic adverse effects in schizophrenia are only partly due to the use of antipsychotics. Schizophrenia itself is associated with higher metabolic complications and cardiovascular mortality [6]. Many patients with schizophrenia are found to have obesity, fasting hyperglycemia, and other metabolic derangements [2].

Topiramate is an anticonvulsant drug used in epilepsy. It is recognized to act on the brain’s glutamate and gamma-aminobutyric acid (GABA) pathways [7]. There are many recent studies showing abnormalities in glutamate and GABA pathways in schizophrenia, such as *N*-Methyl-d-aspartate receptor involvement [8]. Apart from this, topiramate has been shown to be effective in reducing weight in obesity. It is found to be more effective in reducing weight when the patient has a high baseline body mass index (BMI). The effect of topiramate on weight does not seem to depend on the dose of topiramate or the sex of the person [9]. There are two recognized uses of topiramate in schizophrenia. First, topiramate is used as an augmenting agent when there is inadequate symptomatic control in response to antipsychotic treatment. In addition, it is used to reduce weight in patients with schizophrenia [10].

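### Per-visit t tests omit baseline adjustment and leave later dropouts' earlier values out of the month-3 comparison; one repeated-measures model would do modestly better for weight and more for BPRS

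*Protocol article*

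**What the plan says.** Study outcomes in the protocol article defines both outcomes as changes. For the primary: "The primary outcome of the study is changes from baseline values in body weight, waist circumference, and/or skinfold thickness (or BMI"). For the secondary: "The secondary outcome is the change in the symptom score according to the BPRS assessed at three follow-up time points". On timing: "The points of measurement are after the first, second, and third months of the trial period".

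The Data management section then fixes the analysis: "calculations of mean weight differences (primary outcome) and BPRS symptom scores (secondary outcome) will be done at each assessment time point". It continues: "The means will be compared for differences using independent" t tests, and adds that "other relevant statistical analyses will be carried out". On software, the data "will be analyzed using OpenEpi software".

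Three other parts bear on the point. Sample size estimation allows for 20% dropout over three months. Data collection repeats the anthropometric and BPRS assessments at every monthly visit. Eligibility criteria removes from the final analysis the data of any participant given a new psychotropic or certain other drugs during the study.

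**The concern.** The article names its test, so this is a stated choice and not a detail left to an analysis plan. The choice has three weaknesses.

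- **No baseline adjustment.** Weight and BPRS are measured at baseline, but no test uses them as a covariate.
- **Separate visits.** Someone who attends months 1 and 2 and then leaves counts in those two tests but adds nothing to the month-3 test. The earlier values carry information about the missing one.
- **BPRS scale.** Study outcomes says change; Data management says symptom scores. These are different analyses with different precision.

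At stake is some precision at month 3, and protection against bias if people leave because of how their weight or symptoms have already moved. Precision matters for BPRS because the article measures it to detect a possible worsening of symptoms.

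**Working it through.** **1. The plan's own numbers.** 72 analysed, inflated for 20% dropout: 72/(1 − 0.20) = 90, or 45 per arm. This reproduces. Completers per arm at month 3: 45 × 0.80 = 36.

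**2. SD of weight change.** The article gives 2.28 kg (topiramate arm of the earlier trial). Its second calculation (2.75 kg, 80% power, 40 per arm) states no SD. Solving for it at two-sided 5%: 2.75 × √(40/2)/(1.960 + 0.842) ≈ 4.39 kg. Both values are used below. The between-person SD of weight is not given; 8–15 kg is assumed.

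**3. Baseline adjustment alone, weight.** With equal variances at baseline and follow-up, ρ = 1 − SD_change²/(2·SD_weight²), and the variance ratio of the adjusted analysis to the change score is (1 + ρ)/2.

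| SD of change | SD of weight | ρ | Ratio | Variance cut |
|---|---|---|---|---|
| 2.28 | 8 | 0.959 | 0.980 | 2.0% |
| 2.28 | 15 | 0.988 | 0.994 | 0.6% |
| 4.39 | 8 | 0.849 | 0.925 | 7.5% |
| 4.39 | 15 | 0.957 | 0.979 | 2.1% |

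Power for 2.75 kg at 36 per arm with SD 4.39 moves from 75.7% to 76.6–78.9%. With SD 2.28 it is 99.9% either way.

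**4. Baseline adjustment alone, BPRS.** No correlation is given; 0.3–0.8 is assumed. Against change the ratio (1 + ρ)/2 is 0.65–0.90, a cut of 10–35%. Against raw scores the ratio 1 − ρ² is 0.91–0.36, a cut of 9–64%.

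**5. Effective number at month 3 from using all visits.** Assume cumulative losses of 7/13/20%, so 41.85, 39.15 and 36 of 45 are observed at months 1, 2 and 3. With monotone dropout and unit variance, the variance of the month-3 mean is

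V(3|1,2)/36 + [V(3|1) − V(3|1,2)]/39.15 + [1 − V(3|1)]/41.85,

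where V(3|·) is the month-3 variance given the earlier visits. Effective n is its inverse.

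- Correlation 0.8, exchangeable: 0.2889/36 + 0.0711/39.15 + 0.64/41.85 = 0.02513, so 39.8.
- Correlation 0.8, AR(1): 0.36/36 + 0.2304/39.15 + 0.4096/41.85 = 0.02567, so 39.0.
- Correlation 0.5: 37.6 (exchangeable) and 36.9 (AR(1)) by the same formula.

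The t test has 36.

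**6. Simulation of the month-3 estimate** (4,000 runs, 45 per arm, true effect 2.75 kg, weight SD 12 kg, overall dropout 16–21%). Change was generated independently of baseline, so any gain here comes from the earlier visits.

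| Dropout | SD of change | t test on change: bias, SE | Repeated-measures model: bias, SE |
|---|---|---|---|
| Random | 2.28 | 0.00, 0.535 | 0.00, 0.513 |
| Random | 4.39 | 0.05, 1.033 | 0.04, 0.988 |
| Depends on earlier change, both arms | 2.28 | 0.13, 0.512 | 0.00, 0.504 |
| Depends on earlier change, both arms | 4.39 | 0.17, 0.999 | 0.00, 0.984 |
| Placebo gainers leave | 2.28 | 0.33, 0.532 | −0.02, 0.518 |
| Placebo gainers leave | 4.39 | 0.72, 1.002 | 0.01, 0.982 |

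Positive bias (kg) understates the benefit. Under random dropout the SE falls by about 4% and neither method shows material bias (0.05 kg or less). For BPRS (SD 10, correlation 0.5, random dropout), the SE is 2.376 on raw scores, 2.393 on change and 2.054 under the model, about 14% lower than either.

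**The case against.** The other side is strong on size. A t test on change is a valid randomised comparison, and longitudinal modelling is often left to an analysis plan. The first part stands. The second does not dispose of the point, because the article names its test, and the open-ended mention of other analyses commits to nothing.

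A reader might infer several stronger claims that the article does not support.

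- *Baseline weight is ignored.* Study outcomes defines the primary as change, and the natural reading of mean weight differences is that change. Only a comparison of raw weights would be costly: power of 12–31% for 2.75 kg at 36 per arm, with weight SDs of 8–15 kg.
- *Dropouts' early data are wasted.* They are used in the month-1 and month-2 tests and are lost only to month 3.
- *The t tests are biased.* Under random dropout they are not, and dropout that depends only on arm also leaves the difference in means unbiased. The 0.33–0.72 kg above comes from an assumed pattern. If dropout depends on unobserved values, the model can be biased too.
- *Baseline BMI imbalance feeds straight into the result.* The Background does say "It is found to be more effective in reducing weight when the patient has a high baseline body mass index (BMI"). That is a literature statement about who responds more. It matters for a change score only as far as change correlates with baseline, and the model proposed here has no arm-by-baseline term to estimate it.
- *The trial falls short of the 40 per arm in its second calculation.* The article also aims for at least 50 per arm, and 50 × 0.80 = 40. On that aim there is no shortfall; the model's effective number would scale to about 41–44 (36.9 and 39.8 × 50/45).

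Month 3 as the main visit is also a choice made here, since the article lists three visits without ranking them. It fits the 12-week comparison on which the sample size rests.

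**Conclusion.** The point holds as an inexpensive improvement, not as a flaw that invalidates the analysis. For weight the gain is modest: 0.6–2.0% in variance from baseline adjustment with the article's SD of 2.28 kg, 2.1–7.5% with the back-solved 4.39 kg, and an effective month-3 number of about 37–40 instead of 36 per arm from using all visits. For BPRS the adjustment gain is larger, 10–35% against change scores and more if raw scores are compared at correlations above 0.5. The mismatch between scores and change must be resolved in any case. Less bias is to be expected only where dropout depends on values already observed.

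The weight SD, the correlations and the dropout pattern are assumptions; only the 2.28 kg, the 2.75 kg, the 20% and the sample sizes come from the article. The model does not by itself bring back participants whose data are deleted under the new-medication rule.

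**What to change.** In Data management, replace the per-visit t tests with one mixed model for repeated measures on change from baseline in weight. Include arm, month, arm × month, baseline value and baseline × month, with an unstructured covariance. Report the month-3 arm difference with its 95% CI as the main estimate and months 1 and 2 from the same model. Use the same model for BPRS change, so that Study outcomes and Data management agree. Name software that fits mixed models. State how the analysis set relates to the removal rule in Eligibility criteria, since a model on all participants with follow-up and a rule deleting some of them cannot both apply unexplained.

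The cost is slightly more analysis work and a different package. No new data, visits or participants are needed.
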